# Multisession radiosurgery for intracranial meningioma treatment: study protocol of a single arm, monocenter, prospective trial

**DOI:** 10.1186/s13014-020-1478-7

**Published:** 2020-01-30

**Keywords:** Radiosurgery, Multisession radiosurgery, Hypofractionated stereotactic radiotherapy, Intracranial meningioma, Large meningioma, Optic pathway meningioma, Cavernous sinus meningioma, Fractionated radiosurgery, Neurological function preservation

## Abstract

**Background:**

Single session radiosurgery represents a widely accepted treatment for intracranial meningiomas. However, this approach could involve a high risk of treatment-related complications when applied to large volume lesions. In these cases and for those not suitable for surgical resection, radiosurgery in multisession setting could represents a viable option. The literature results are reassuring in terms of correlated adverse events as well as in terms of tumor control. However, no prospective long-term results are available. In this scenario, we design a prospective monocentric phase II study, in order to verify the safety of a multisession radiosurgery schedule delivering 25 Gy in 5 daily fractions.

**Methods:**

Patients diagnosed with large and/or near to critical structures, intracranial meningiomas have been treated by means of multisession radiosurgery in both exclusive and postoperative settings. The primary study aim is safety that has been being prospectively scored based on international scales, including NCI Common Toxicity criteria, version 4.03, Barrow Neurological Institute pain intensity score, Barrow Neurological Institute facial numbness score and House-Brackmann Facial Nerve Grading System for qualitative analysis. Secondary aim is treatment efficacy in terms of local control that has been being assessed on volumetric analysis.

**Discussion:**

This is the first prospective phase II trial on multisession radiosurgery for large and/or near to critical structures intracranial meningiomas. If positive results will be found, this study could represent the starting point for a phase III trial exploring the role of multisession radiosurgery in the exclusive and postoperative radiation therapy treatment of intracranial meningiomas.

**Trial registration:**

Trial registration: clinicaltrials.gov platform (Multisession Radiosurgery in Large Meningiomas –MuRaLM- identifier NCT02974127). Registered: November 28, 2016. Retrospectively registered, https://clinicaltrials.gov/ct2/show/NCT02974127?term=radiosurgery&cond=Intracranial+Meningioma&draw=2&rank=1

## Background

Radiosurgery is a precise therapeutically effective radiation dose to an imaging-defined target [1]. Single session radiosurgery (sRS) represents the gold standard treatment for small and medium volume intracranial benign meningioma not suitable for surgical removal. The literature results ranged from 87% [2] to 100% [3, 4] in terms of both clinical stabilization and tumor growth control after 5 years from sRS. The treatment-related complications are also reassuring with low reported rates [5–7]. However, intracranial meningiomas are often close to critical structures or diagnosed when the volume is already large. In these cases, sRS could involve a high risk of treatment-related adverse effects, whereas multisession radiosurgery (mRS) can represent a viable treatment option as both exclusive and postoperative approach. By now, several retrospective studies focused on mRS for intracranial meningiomas have been published and all of them have reported promising results [8–13]. Although the effects are mostly encouraging, only long-term follow-up is able to investigate the impact of mRS in benign intracranial meningioma outcomes.

In this scenario, in 2011 we designed a prospective observational study to evaluate the safety and efficacy of radiosurgical multisession approach for treatment of both large and close to critical structures intracranial meningiomas. This phase II protocol can be appropriate to determine whether the multisession approach is worth to be studied through a phase III trials in the exclusive irradiation setting.

## Methods and design

### Study design

This is an observational phase II, prospective, monocenter, single-arm study focused on mRS for both large and/or close to critical structures intracranial meningiomas. Based on preliminary results, [8–12, 14] we hypothesized that a schedule of mRS delivering 25 Gy in 5 daily fractions could achieve a good local control and at the same time a low toxicity rate for large and/or critically located intracranial meningioma (lesions with a maximum diameter about or superior to 3 cm and/or located at around less than 3 mm from critical structures, e.g. near to chiasm, optic nerve, brainstem).

### Ethics

The Institutional Ethical Committee Board approved (2011 August 11th, number 415/2011) the study protocol, the declaration of Informed Consent and all case report forms (CRFs). The specific informed consent was provided and illustrated to each patient before the enrollment. This trial was registered to clinicaltrials.gov platform (Multisession Radiosurgery in Large Meningiomas –MuRaLM- identifier NCT02974127). We have been conducting it according to the principles of the Declaration of Helsinki and in accordance with the Medical Research Involving Human Subjects Act.

### Recruitment

Eligible patients who present at the Unit of Radiation Oncology of our Institute were recruited to the study. Eligibility requirements were:

### Inclusion criteria

Patients with radiological or histological diagnosis of large intracranial meningioma and/or critically located, then not suitable for sRS were eligible for our study. Other inclusion criteria were age ≥ 18 years old, KPS ≥ 70 and written informed consent.

### Exclusion criteria

Refusal of the patients to take part in the study; pregnant or lactating women; allergy to contrast medium; neurofibromatosis type II (NF2) diagnosis; atypical and malignant histologically confirmed meningiomas; diagnosis of optic sheath meningioma; and patients who had received prior radiotherapy at the same site.

### Dropout criteria

Criteria that will lead to the dropout of a patient before completion of this study may be any kind of treatment for medical reasons or impairment that will result in an interruption of radiotherapy. Furthermore, the patient’s desire to exit the study or withdrawal of consent as well as any unexpected serious adverse event (SAE) occurring during treatment or in follow-up that leads to early completion of the study will result in drop-out.

### Study aims and endpoints

The main aim is to evaluate the safety of the mRS in terms of prospectively scored adverse events (AEs), defined as stability or improvement of preexisting neurological deficits or as absence of new neurological deficits after irradiation. The secondary aim is to evaluate tumor response in terms of local control (LC), defined as stability or reduction of lesion volume.

### Assessment of the primary and secondary endpoints

#### Pretreatment evaluation

Pre-treatment evaluation comprises history taking interview, physical and neurological examination and radiological record evaluation. Karnofsky performance status (KPS) (Additional file 1: Appendix I), any prior brain surgery and/or brain radiation therapy have been registered. Moreover, when lesion involved optic pathways and steato-acoustic nerves, ophthalmological and/or audiometric evaluations were required.

As part of neurological examination, cranial nerve function has been recorded. For trigeminal nerve function assessment two parameters were used: the semi quantitative scales Barrow Neurological Institute pain intensity score (BPS) and Barrow Neurological Institute facial numbness score (BNS) [15]. The facial nerve function assessment was based on House-Brackmann (H-B) Facial Nerve Grading System for qualitative analysis [16]. For acoustic sensorineural assessment, two evaluations were registered: speech discrimination and audiometric threshold. For optic pathways assessment at least a bilateral visual field analysis and a visual acuity measurement were required. Any other deficits were recorded.

Table 1 summarizes prescribed pre-treatment investigations.

**Table 1 Tab1:** Required pre-treatment investigations

Investigations	
Clinical history and physical exam	Clinical history, prior therapies, drug use, neurological examination
Hematology	Hemoglobin, white blood count, platelet count, creatinine
Adverse events	Baseline adverse event (baseline neurological symptoms and any post-surgery adverse events) recorded according to NCI CTCAE v. 4.0
KPS	See appendix 1
Visual acuity	
Visual field	
Speech discrimination	
Audiometric threshold	
BNS/BPS	
House Brackmann	
Radiology	Volumetric (1–3 mm thin slices) gadolinium-enhanced MRI

For unoperated patients the diagnosis of benign meningioma was clinical and radiological and was made by clinicians and expert neuroradiologists based on magnetic resonance imaging (MRI) and on additional computed tomography (CT) when required.

#### Follow-up evaluation

Patients have been being prospectively followed within the trial protocol after treatment for 5 years at least.

Post-treatment evaluations consist of neurological assessment as detailed before, audiometric evaluation and/or visual function assessment if required. Each AE has been being scored in accordance with the NCI Common Toxicity criteria, version 4.03 [17]. For local control follow-up, a gadolinium-enhanced thin slice (1 to 3 mm) brain MRI is required and T1-weighted volumetric post contrast sequence is mandatory as well as post contrast fat-saturation when anterior skull base lesion is under evaluation. To assess the tumor response, a volumetric analysis has been being performed by means of co-registration of each follow-up MRI on baseline MRI and contouring of the lesion on each post-treatment MRI, in order to ensure that the PTV and the post-irradiation lesions become spatially aligned and comparable.

Patients are scheduled for follow-up visits after 4 months from the treatment, every 6 months during the first 2nd and the 3rd years and thereafter every 12 months.

Tumor response has been defined and classified according to the following criteria:
Complete response (CR) as a tumor disappearance.Partial response (PR) as ≥20% decrease in the tumor volumetric size.Stable disease (SD) as no change or any change different from the previous ones in tumor size.Progressive disease (PD) as increase in any tumor volumetric size outside the PTV or increase of tumor volume ≥ 20% confirmed at least on two consecutive MRI.

A checklist assessment has been constructed and reported in Table 2. The neurological assessment is detailed in Table 1.

**Table 2 Tab2:** Intervention and assessment schedule for the MuRaLM trial

		Follow up			
Parameters	Recruitment	4 months	8 months	12 months	Every control
History, physical exam	X				
KPS	X	X	X	X	X
Neurological deficit assessment	X	X	X	X	X
AEs	X	X	X	X	X
Volumetric MRI/CT	X	X	X	X	X
Informed consent	X				

If death occurs or patients leave the study prior to 5 years, they are still included into the intention-to-treat population.

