### Treatment planning and radiation technique

The mRS treatments were performed as previously described [19]. Briefly, the targets was delineated on high-resolution (1 mm thickness) contrast-enhanced computed tomography (CT) and on co-registered high-resolution MRI (1 mm thickness), using always T1 and T2-weighted contrast-enhanced sequences and when needed also using fat-saturated sequences. The tumour volume (TV) was identified based on these images as contrast-enhancing areas. We did not add any margins for clinical target volume (CTV) nor for planning target volume (PTV). Therefore, the PTV, CTV and TV (or GTV, gross tumour volume) were the same. All anatomical structures were contoured as organs at risk (OARs): brain, brainstem, retinas, eyes, lenses, optic nerves, optic pathways, cochleas, acoustic nerves, and skin. Organs at risk were contoured and adapted based on both CT scans and MRI.

The treatment plans were performed with an inverse planning method using non-isocentric technique (Multiplan Accuray Inc.). Based on literature data, [8–12, 14] we prescribed a dose of 25 Gy in 5 daily fractions to the isodose line encompassing 95% of the PTV (80% ± 5% prescription isodose line). We have considered as maximum dose to the OARs the prescription dose (25 Gy) at no more than 1 cc of the organ volume (D1cc ≤ 25 Gy). Unfortunately, no cognitive tests have been delivered. For this reason we did not analyzed the hippocampal dose for the analysis. The evaluation of setup and positioning verification was performed with an image-guided, real-time tracking system. According to our protocol, prophylactic dexamethasone (4 mg p.o. from the first day of treatment) was orally administered to all patients, unless they had some contraindications (e.g. insulin therapy). The patients maintained it and tapered it off during the 3 weeks following treatment. An H2-receptor antagonist was given in association with dexamethasone.

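### With a zero-margin PTV, counting any increase outside the PTV as progression makes the 20% threshold redundant and leaves no room for stable disease with growth below 20%

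*Protocol article*

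**What the plan says.** The secondary aim is "local control (LC), defined as stability or reduction of lesion volume" (protocol article, Study aims and endpoints). Follow-up evaluation sorts response into four classes. The last, progressive disease, is "increase in any tumor volumetric size outside the PTV", with the alternative of an "increase of tumor volume ≥ 20% confirmed at least on two consecutive MRI". Stable disease is a residual class. The same section has each follow-up MRI co-registered to the baseline MRI and the lesion contoured again, so that it can be compared spatially with the PTV.

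Treatment planning and radiation technique fixes what the PTV is. On the tumour itself: "The tumour volume (TV) was identified based on these images as contrast-enhancing areas". On margins: "Therefore, the PTV, CTV and TV (or GTV, gross tumour volume) were the same".

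The article gives no minimum volume or distance for the out-of-PTV criterion. It names no reference other than the baseline MRI.

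**The concern.** Each rule is reasonable alone, but together they conflict. A 20% threshold is there so that small volume changes count as stable. An out-of-PTV criterion with no threshold can coexist with it only if the PTV is larger than the tumour, or if the criterion is meant for tumour away from the treated lesion. Here the PTV is the tumour, and the text does not limit the criterion to separate disease.

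Local control is the trial's only efficacy endpoint. Under Sample size and statistical analysis it is estimated at 5 years with a 95% confidence interval and analysed by Kaplan-Meier and Cox methods. A reader who applies the criteria literally and one who applies the 20% threshold could classify the same scans differently and date the events differently. The Discussion also expects the volumetric analysis to inform the debate on how tumour response should be assessed, which makes the definition matter more.

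**Working it through.** **The plan's own figure.** The only sample size in the article is for toxicity. With p0 = 0.20, p1 = 0.12, one-sided 5% and 80% power, the score test gives n = [(1.645·√(0.20·0.80) + 0.842·√(0.12·0.88))/0.08]² = 135.6, so 136. Then 136/0.80 = 170, as stated. It does not depend on the progression criteria. No power figure is given for local control.

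**Inputs for this point.**
- Margin from tumour to PTV: 0 mm (Treatment planning and radiation technique).
- Volume threshold: 20% (Follow-up evaluation).
- Threshold for the out-of-PTV criterion: none (Follow-up evaluation).
- Lesion size for illustration: 3 cm diameter, the size named in Study design, taken as a sphere. The spherical shape is an assumption.

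**Step 1: logic.** Let V0 be the baseline tumour volume, equal to the PTV, and V1 the follow-up volume. Tumour outside the PTV at baseline is 0 by construction. A lesion lying wholly inside the PTV has V1 ≤ V0. So if V1 > V0, some tumour is outside, and the amount outside is at least V1 − V0. Hence:
- any net growth over baseline meets the out-of-PTV criterion;
- every increase of 20% or more over baseline meets it too, so the 20% criterion adds no case;
- growth between 0 and 20% is progression, taking progression to override the residual stable class.

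This step does not need the sphere.

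**Step 2: size.** For radius r = 15 mm, V0 = (4/3)π·15³ = 14.14 cc.
- Growth per side for +20%: 15·(1.2^(1/3) − 1) = 0.94 mm.
- Growth of 0.25 mm per side: (15.25/15)³ − 1 = 5.1%.
- Growth of 0.5 mm per side: (15.5/15)³ − 1 = 10.3%, which puts 14.14 × 0.103 = 1.46 cc outside the PTV.

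The last two are progression by the first criterion and not by the second. For a 5 cm sphere the 20% criterion needs 1.57 mm per side, and 0.5 mm per side is +6.1%.

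**Step 3: displacement without growth.** For equal spheres offset by d, the fraction outside is 0.75(d/r) − (d/r)³/16. At r = 15 mm, offsets of 0.5, 1 and 2 mm give 2.5%, 5.0% and 10.0%; the 1 mm offset is 0.71 cc. These offsets are assumed, because the article reports no registration or contouring error.

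**The case against.** The strongest reply is that the two criteria were meant for different things: the first for marginal or out-of-field tumour, the second for the treated lesion. That may be the intention, but the text does not say so. Nor is this just detail left to a fuller protocol, since two rules that are stated conflict when followed.

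A reader might go further than the text allows in several ways.
- **That the 20% criterion can never operate.** This depends on measuring from baseline. If growth were measured from the smallest post-treatment volume, regrowth inside the old PTV could meet the 20% criterion alone. No such reference is stated, so the redundancy holds on the text, conditionally.
- **That the first criterion needs no confirmation.** No punctuation settles this; the closing phrase can govern both criteria. If it does, isolated reading differences matter less, but confirmed growth of any size is still progression.
- **That a pure shift counts as progression.** The wording requires an increase, and a displaced contour of unchanged volume is not plainly one. Step 3 shows only what is possible under a strict spatial reading.
- **That local control would measure mainly contouring noise.** The documents give no error size. Follow-up asks that "a gadolinium-enhanced thin slice (1 to 3 mm) brain MRI is required", against 1 mm planning images, but Table 1 allows the same 1 to 3 mm range for the pre-treatment MRI, and a volumetric post-contrast sequence is mandatory at follow-up.
- **That the result could not be compared with the 87% to 100% in the Background.** The analysis section plans no such comparison, and that range concerns single-session treatment.

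It is also fair to say that the endpoint is secondary, and that the article does not tie the phase III decision to local control specifically.

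**Conclusion.** The conflict stands. With no margin and baseline as the reference, the out-of-PTV criterion absorbs the 20% criterion, and growth below 20% cannot be stable disease. On a 3 cm sphere, the band of growth from 0 to 0.94 mm per side changes class depending on which criterion is followed. The conclusion rests on three assumptions: the PTV serves as the baseline contour, the 20% is measured from baseline, and progression overrides the residual stable class.

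The scope of confirmation is ambiguous. If it excludes the first criterion, a single contouring or registration difference could count as progression; how often cannot be derived from the documents. The consequence is confined to local control: its 5-year estimate and its Kaplan-Meier and Cox analyses. The primary toxicity test and N = 170 are unaffected.

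**What to change.** Reconcile Follow-up evaluation with Treatment planning and radiation technique:
1. For the treated lesion, define progression as an increase of at least 20% in total contoured volume over a stated reference (baseline), wherever the growth lies.
2. Restrict the out-of-PTV criterion to new or out-of-field tumour, or to growth beyond a prespecified tolerance justified by the trial's own registration and contouring error. A tolerance of 3 mm, the largest permitted slice thickness, is only an example. On a 3 cm sphere, uniform growth of 3 mm is (36/30)³ − 1 = 73%, so such a tolerance would matter only for focal growth.
3. Apply the two-MRI confirmation to both criteria.
4. Record the site of failure, inside or outside the PTV, as a descriptor.

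Patients have already been treated in this single-arm study, so the rule should be fixed before local control is analysed. Local control under the published wording, read literally, should be reported as a sensitivity analysis.

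The work is a wording change and reclassification from existing contours. There are two costs. Small marginal growth would be called later, and visits are 12 months apart after year 3. The revised rule can also only leave local control unchanged or raise it, which is why both results need to be shown.

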### Data collection

Based on General Data Protection Regulation (GDPR) guidelines, to ensure privacy respect during the clinical trial processes, an identification number has been provided for each patient. Clinical, neurological and radiological data has been being recorded on a case report form (CRF) and on an electronic database according to the good clinical practice guidelines (GCP) at baseline and in the follow-up period at each scheduled consultation [18].

### Sample size and statistical analysis

Assuming a one-sided score z test type I error of 5%, a power of 80%, an expected toxicity of the mRS at 5 years of 12% (H1, alternative hypothesis) vs a null hypothesis of 20% (H0), and assuming a loss to follow-up of no more than 20%, a sample of 170 patients is needed.

A description of patient characteristics at baseline will be provided in terms of percentages for dichotomous data, and means with standard deviations and medians with value ranges for continuous data. Primary analysis will be based on the score z test. Proper estimates with the corresponding 95% confidence intervals will be provided for primary and secondary outcomes at 5 years. Additionally, primary and secondary outcomes will be also analyzed as time to event variables using Kaplan-Meier method and Cox proportional hazards model (to adjust for potential confounders). STATA statistical software, version 15 (StataCorp. 2017. Stata Statistical Software: Release 15. College Station, TX: StataCorp LLC) will be used for the statistical analysis.

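### The additional Kaplan-Meier analysis of toxicity and progression has no place for death as a competing event, so its 5-year risks would sit slightly high (minor)

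*Protocol article*

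**What the plan says.** The section on sample size and statistical analysis in the protocol article sets out three layers.

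- The confirmatory layer is a one-sample test of the 5-year toxicity proportion, 12% expected against 20% under the null: "Primary analysis will be based on the score z test".
- A separate sentence promises estimates with 95% intervals for both outcomes at 5 years and names no estimator.
- A further sentence, introduced as additional, says that "primary and secondary outcomes will be also analyzed as time to event variables using Kaplan-Meier method", with a Cox model to adjust for confounders.

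The section on study aims and endpoints defines safety by new or worsened neurological deficits and local control by lesion volume. The response criteria under follow-up evaluation define progression by tumour growth. Death is part of none of these definitions. The same follow-up section says: "If death occurs or patients leave the study prior to 5 years, they are still included into the intention-to-treat population". The article does not say how a death enters the time-to-event analysis, and it mentions neither competing risks nor cumulative incidence.

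**The concern.** A patient who dies can no longer develop a deficit or show tumour growth, so death competes with both outcomes. Kaplan-Meier knows one event type and censoring. Since death is not part of either event, the usual way to run the named analysis is to censor deaths. That treats the deceased as if they still carried the risk of the patients who remain under observation, and one minus Kaplan-Meier then estimates the risk in a hypothetical setting without death.

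The planning hypotheses speak of toxicity at 5 years as a proportion, most naturally the share of treated patients who actually experience it. The curve would therefore describe a somewhat different quantity from the one the trial was designed around, and would show toxicity slightly too high and local control slightly too low. What is at stake is the descriptive long-term picture, which the article wants to use in deciding on a phase III trial. The test decision is not at stake.

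**Working it through.** **Step 1: reproduce the plan's own figure.** Inputs from the sample size section: one-sided type I error 5%, power 80%, null 20%, alternative 12%, loss to follow-up at most 20%.

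n = [z(0.95)·√(0.20·0.80) + z(0.80)·√(0.12·0.88)]² / (0.20 − 0.12)²

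= [1.645·0.400 + 0.842·0.325]² / 0.0064 = (0.658 + 0.273)² / 0.0064 = 135.6 (unrounded inputs), rounded up to 136.

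Allowing for loss: 136 / 0.80 = 170. This matches "a sample of 170 patients is needed". The calculation uses a proportion and no survival curve, so the choice of time-to-event estimator does not enter it.

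**Step 2: size of the Kaplan-Meier excess.** The documents give no mortality, so it is assumed and varied. With constant cause-specific hazards, let h and d be the cumulative 5-year hazards of the event and of death.

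- Actual cumulative incidence: F = h/(h + d) · [1 − exp(−(h + d))]
- One minus Kaplan-Meier with deaths censored: K = 1 − exp(−h)

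Mortality can be expressed in two ways:

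- (a) 5-year mortality m, with d = −ln(1 − m), and h solved from the equation for F.
- (b) 5-year risk D of dying before the event, with h + d = −ln(1 − F − D) and h = (h + d)·F/(F + D).

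Example for F = 12% and 10% mortality. Under (a), d = 0.1054, h = 0.1350 and K = 1 − exp(−0.1350) = 12.6%. Under (b), h + d = −ln(0.78) = 0.2485, h = 0.2485·0.12/0.22 = 0.1355 and K = 12.7%.

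| Assumed mortality | K if true toxicity is 12%, (a) | K if true toxicity is 12%, (b) |
|---|---|---|
| 2% | 12.1% | 12.1% |
| 5% | 12.3% | 12.3% |
| 10% | 12.6% | 12.7% |
| 15% | 13.0% | 13.1% |
| 20% | 13.4% | 13.5% |

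The two versions agree within about 0.1 point. For a true toxicity of 20%, version (a) gives 20.2%, 20.5%, 21.0%, 21.6% and 22.2% over the same range.

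**Step 3: progression.** The background section cites 87% to 100% control at 5 years after single-session treatment, so failure risks up to 13% are a plausible range. Under (b), a true 5% reads 5.05% at 2% mortality and 5.6% at 20%. A true 13% reads 13.1% and 14.6%.

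**Step 4: scale.** The standard error of a 12% proportion in 136 patients is √(0.12·0.88/136) = 2.8 points. An excess of 0.1 to 0.7 points is at most about a quarter of that.

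**The case against.** The strongest case against runs as follows.

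- **The method is only additional.** This stands. A reader might infer that the trial's 5-year toxicity result, or its test against 20%, is biased. The text does not support that: the test is the score z test, and Kaplan-Meier comes afterwards. Nor can one say that the promised 95% intervals are centred on the wrong value, because the sentence promising them does not name Kaplan-Meier.
- **The article never says that deaths are censored.** This is literally true, and the rule may stand in a fuller document. But the article does name the estimator and does define the events without death. Counting deaths as events would contradict those definitions, and keeping the deceased at risk to 5 years is not standard and is not stated. Censoring is the natural reading, though still an inference.
- **The bias is small.** This stands. Patients need a KPS of at least 70, and histologically confirmed atypical and malignant tumours are excluded. On the other hand there is no upper age limit, and follow-up lasts at least 5 years.
- **The net direction is open.** This stands. Under the dropout criteria, an unexpected serious adverse event that ends participation makes the patient a drop-out. If such patients are censored before a toxicity is counted, the curve could run too low. That is a separate problem. It can offset the effect of death but does not remove it.
- **The simple proportion may not be the cumulative incidence either.** This also stands. The article does not say how lost or deceased patients enter the denominator, so one cannot claim that the curve and the proportion must disagree in a fixed way.
- **The error would work against the treatment.** This is correct for the death component, which overstates toxicity and understates control. It could not by itself produce a false claim of safety.

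**Conclusion.** The point holds as a minor one. For the additional time-to-event analysis, the article names an estimator that does not fit its own endpoint definitions once deaths occur, and it expects deaths. If deaths are censored, the Kaplan-Meier-based 5-year risks lie above the actual cumulative risks by about 0.1 to 0.7 percentage points on 12% at an assumed 2% to 10% mortality, and by about 1.4 points at 20%. These figures rest on constant hazards and on mortality that the documents do not supply. They isolate the effect of death and do not predict the net bias of the reported curve. The primary test and the 170 patients stand as they are.

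**What to change.** In the sample size and statistical analysis section, replace Kaplan-Meier for toxicity and for progression by the cumulative incidence function (Aalen-Johansen estimator) with death as a competing event, and report its 5-year value with a 95% interval. State that the Cox model is interpreted as cause-specific. If deaths are censored it already is, so this only makes the label explicit. Keep Kaplan-Meier for outcomes that include death, such as progression-free survival.

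The cost is one or two sentences and slight extra analysis work. Dates of death must be available. The intention-to-treat sentence presupposes that deaths become known, but the assessment schedule in Table 2 has no separate entry for them, so this should be checked. The sample size and the primary test need no change. The new estimator does not settle how drop-outs after serious adverse events are handled, since it too assumes that censoring is uninformative.
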